#### Study recruitment and enrollment

Based on Healthy Lifestyles visit data (800 new patients/year) and pilot study data (100 subjects 5–12 years of age recruited in 9 months), we estimate that we can conservatively screen 500 subjects and enroll 270 in a 2-year enrollment period. We continuously monitor recruitment to ensure equal distribution among age groups, and plan to apply a stratification scheme if groups become imbalanced. As of April 2020, we have enrolled 261 children, with recruitment continuing through June 2020.

Primary care providers will refer eligible subjects using a novel Best Practice Alert (BPA, Epic) automatically generated by pre-specified inclusion criteria, and confirmed by a trained research assistant (Table 1). The BPA “fires” during the patient’s annual visit, and the pediatrician can click “ok to contact” or “opt out,” and this response enters a call list for the research staff to schedule the study visit. If the patient agrees to attend the study visit, the research coordinators complete the consent process with parents and assent with children, as approved by the Duke Health Institutional Review Board.

**Table 1 Tab1:** Inclusion, Exclusion, and Opt-out Criteria

Inclusion Criteria	
• Child age 5–18 years • Child body mass index ≥95th percentile • Parent can speak and read in English or Spanish • Parent ownership of a device that is able to receive and send text messages	
Exclusion Criteria	
• Live farther than a 20-mile radius from the Bull City Fit program site • Endogenous or genetic cause of obesity • Taking a medication that causes weight gain • Participation in a pediatric weight management program within 12 months • Parent or child significant health problem that would limit participation • Pregnancy in patients of child-bearing age	
Opt-out Criteria	
✓ Primary care physician opts patient out of study for reasons including: severe obesity (BMI > 160% of sex- and age-specific 95th percentile), urgent co-morbidities, parental unwillingness to be contacted by a research assistant, or at physician clinical judgment.	

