### Measurement strategy

#### Trial measures

##### Body mass index:

The primary study outcome is BMI obtained through standardized measures of body weight and height using a digital scale and stadiometer [43]. Measures will be obtained at all data points. A large number of children referred to the healthy lifestyles clinic have a BMI significantly greater than the 95th percentile, and known challenges exist in measuring changes in BMI at extreme values. Therefore, as recommended by Flegal et al. we will assess and report child relative BMI, expressed as a standard deviation score (zBMI) and as a percent of the BMI value at the 95th percentile (%95th BMI) to evaluate and track obesity [44].

Cardiorespiratory Fitness is the principal secondary outcome, and will be assessed by heart rate at the completion of the YMCA submaximal bench-stepping test [45]. This was chosen over others due to its sensitivity to fitness-related changes in heart rate and ease of implementation in a mobile setting.

Given the complexity of pediatric obesity, a variety of secondary outcomes, including cardiovascular measures, social and emotional health, and behaviors, will also be assessed. Blood pressure will be measured with a calibrated auscultatory sphygmomanometer in the seated position with an appropriately sized cuff using standard methods [46]. Fasting blood sample for cardiometabolic biomarkers, including lipids, glucose, and transaminases will be obtained. Body fat percent will be measured using calibrated bioelectrical impedance. Parent BMI will be directly measured from parent height and weight using calibrated stadiometers.

Weight-specific quality of life will be measured using the validated “Sizing Me Up” child obesity-specific instrument, which has been used previously in the Healthy Lifestyles clinic population [47]. Research staff will administer survey-based instruments to the parent, child, or both to assess child temperament, mood, peer relationships, perceived family support, and body-esteem. We will employ measures developed by NIH PROMIS®, a patient-reported outcomes data management system to encourage more universal measurement of clinical outcomes across studies [48]. PROMIS is a data management system that allows researchers to choose independently validated items from domain-relevant item banks.

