### Statistical analysis plan

#### Sample size

Preliminary data suggests that a meaningful difference in mean 6-month zBMI is − 0.10, and the pooled standard deviation across intervention groups is 0.2 [74]. We assume that 30% of subjects will be lost to follow-up prior to 6 months. Assuming normality of 6-month zBMI, power was computed using a two-sided t-test considering a type I error rate α = 0.05. In total, 270 subjects are needed to have 80% power to detect the meaningful difference in zBMI.

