#### General analytic approach

To determine the effect of the intervention on 6 month change in zBMI, a generalized estimating equation model will be fit to estimate the difference in mean change in BMI between intervention groups, using an intention-to-treat approach [75]. This model will account for repeated observations of each child as well as correlation between siblings. A similar model will be used to assess the effect of the intervention on cardiorespiratory fitness as measured by heart rate at 3 min during the step test.

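### The stated primary contrast is a difference in mean change with no baseline adjustment stated; adjusting for baseline zBMI would cost nothing and be at least as precise

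*Protocol article*

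**What the plan says.** *General analytic approach* sets out the primary analysis. It opens with the effect on 6-month change in zBMI, then states that "a generalized estimating equation model will be fit to estimate the difference in mean change in BMI between intervention groups", by intention to treat. The same sentence therefore names the outcome once as zBMI and once as BMI. The model is said to allow for repeated observations on a child and for correlation between siblings. No other model term is given.

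*Sample size* works on a different quantity. It says that "a meaningful difference in mean 6-month zBMI is" −0.10 and that "the pooled standard deviation across intervention groups is 0.2". The calculation is introduced by "Assuming normality of 6-month zBMI", and "power was computed using a two-sided t-test considering a type I error rate" of 0.05. With 30% loss before 6 months, it concludes that "270 subjects are needed to have 80% power to detect the meaningful difference in zBMI".

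Table 2 schedules child BMI at baseline and at every later visit. Age is an eligibility criterion in Table 1. Both baseline zBMI and age group are therefore available for every child.

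**The concern.** Read as written, the primary estimate is the mean change in one arm minus the mean change in the other. That contrast fixes the coefficient on baseline at 1. Because of regression to the mean, the coefficient that minimises the variance is usually below 1. Fixing it at 1 gives away precision and over-corrects whatever baseline difference chance has produced.

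At stake are the width of the interval for the primary effect and a small conditional shift in the estimate. There is also a clarity problem: the trial is powered on a 6-month level and analysed on a change, and the standard deviation of 0.2 is not clearly tied to either.

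**Working it through.** **The plan's own figure.** Inputs from *Sample size*: difference 0.10, SD 0.2, two-sided α 0.05, power 80%, 30% loss. Allocation is 1:1 (*Randomization*).

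- n per arm = 2 × (1.960 + 0.842)² × (0.2/0.10)² = 62.8, so 63 per arm and 126 in total. Then 126/0.7 = 180.
- The exact t-test gives 64 per arm, 128 in total, and 128/0.7 = 183 after rounding up.
- The stated 270 is not reproduced; it is larger than its inputs require. With 270 enrolled and 30% lost, 270 × 0.7/2 = 94.5 per arm remain. The SE is 0.2 × √(2/94.5) = 0.0291, 0.10/0.0291 = 3.44, and power is Φ(3.44 − 1.96) ≈ 93%.

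**Change score against baseline adjustment.** Let s₀ and s₁ be the baseline and 6-month SDs and r their correlation.

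- Var(change) = s₀² + s₁² − 2r·s₀·s₁
- Var(adjusted) = s₁²(1 − r²)
- Difference = (s₀ − r·s₁)², which is never negative. Apart from the one degree of freedom spent on the slope, adjustment cannot be less precise.
- With s₀ = s₁ = s, these become 2s²(1 − r) and s²(1 − r²), with ratio (1 + r)/2. The SE ratio is √((1 + r)/2).

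**Residual from chance imbalance.** If the arms differ by D at baseline, the expected 6-month difference is the effect plus rD. Subtracting D leaves the effect minus (1 − r)D. Taking 0.2 as the zBMI SD and 94.5 per arm, a one-SE imbalance is D = 0.029.

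The documents do not give r, so it is assumed over a range:

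| r (assumed) | Variance ratio | SE ratio | Over-correction, (1 − r) × 0.029 |
|---|---|---|---|
| 0.5 | 0.75 | 0.866 | 0.015 |
| 0.7 | 0.85 | 0.922 | 0.009 |
| 0.8 | 0.90 | 0.949 | 0.006 |
| 0.9 | 0.95 | 0.975 | 0.003 |
| 0.95 | 0.975 | 0.987 | 0.001 |

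**Effect on power, 94.5 per arm.**

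- If 0.2 is the SD of change, the change-score analysis has 93.0% power. The adjusted analysis has 97.8%, 96.1%, 95.2%, 94.1% and 93.6% down the table.
- If 0.2 is the SD of 6-month zBMI, change-score against adjusted power is 93.0% against 97.8% at r = 0.5 and 99.3% against 99.8% at r = 0.7. Both are about 100% from r = 0.8.
- On this second reading the change score keeps 80% power as long as its SD is at most 0.245. Solving 0.2 × √(2(1 − r)) = 0.245 gives r ≈ 0.25, well below the range considered.

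**The case against.** The strongest reply is that this is a short paragraph in a condensed article. It never calls the model unadjusted, and covariate lists usually sit in an analysis plan that is not shown here. Nor does a difference in mean change settle the estimator. Regressing change on arm and baseline gives the same arm effect as analysing the 6-month value adjusted for baseline. A repeated-measures GEE that carries baseline as a response, with a common baseline mean and a suitable working correlation, recovers nearly the same precision. This stands in part: the text does not show that baseline or age is excluded, and an absent covariate list is no fault in itself. What remains is that the article does state a contrast, and that contrast, run as described, is the less precise one.

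It is also fair to say that the gain is small if r is high, and that a change contrast in a randomised trial is unbiased over randomisation. Both stand.

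Three stronger readings are tempting and unsupported.

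- A reader might infer that chance imbalance in zBMI goes uncorrected. It does not: subtracting baseline removes it and overshoots by the fraction 1 − r.
- A reader might take the remark in *Body mass index* that "known challenges exist in measuring changes in BMI at extreme values" as an admission that baseline severity belongs in the model. The article draws a different consequence from it, namely reporting zBMI and percent of the 95th percentile. It concerns the choice of metric.
- A reader might take the "plan to apply a stratification scheme if groups become imbalanced" in *Study recruitment and enrollment* as a late remedy for imbalance between arms, with 261 of 270 already enrolled. The sentence more naturally concerns recruitment across age groups, which fits the age-specific biospecimen targets. Covariate adjustment could not replace that.

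**Conclusion.** The point holds as a modest improvement that costs nothing. The stated contrast is valid but can be matched or bettered in precision by using a measurement that every child already has. The adjusted SE is about 0.87 of the change-score SE at r = 0.5, 0.95 at r = 0.8 and 0.99 at r = 0.95. The residual from a one-SE baseline imbalance is 3% to 15% of the 0.10 target for r from 0.9 to 0.5.

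These sizes rest on an assumed r, on equal variances at baseline and 6 months and, for the residual, on reading 0.2 as the zBMI SD with 94.5 per arm. The calculation ignores sibling clustering and the 3-month visit.

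A reader might conclude that the trial is biased or underpowered. The documents do not support this: randomisation protects the contrast, and the stated inputs already give about 93% power. The mismatch between a level in *Sample size* and a change in *General analytic approach*, and between zBMI and BMI within the latter, is in the text itself and does not depend on r.

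**What to change.** In *General analytic approach*, state the primary estimate as the between-arm difference in 6-month zBMI from the GEE, adjusted for baseline zBMI and age group and clustered by household. Name zBMI throughout that sentence. Report the unadjusted difference in mean change as a sensitivity analysis.

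With baseline zBMI as a covariate, the adjusted difference in 6-month level and the adjusted difference in change are the same number, so the mismatch with *Sample size* disappears. It would help to say there whether 0.2 is the SD of 6-month zBMI or of change.

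Leave the recruitment-monitoring sentence in *Study recruitment and enrollment* as it is. The cost is wording only: no new data, visits or children are needed.

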#### Statistical analysis of biospecimens

We will analyze four primary phenotypes: (1) obese vs. lean pediatric individuals (combining children and adolescents); (2) relative BMI as a continuous trait; (3) baseline cardiorespiratory fitness measures; and (4) obese vs. lean comparisons that are different in children vs. adolescents. Analyses will be corrected for multiple comparisons using False Discovery Rate (FDR) adjustment at the level of each individual platform or at the level of number of factors for the integrated ‘omics analyses. The results of these analyses will inform which patient stool samples will be used for gnotobiotic mouse experiments, and what traits to monitor in recipient gnotobiotic mice. We will also perform sensitivity analyses restricted to children and adolescents with clinical features similar to children who had the greatest relative BMI reduction. Power calculations for individual metabolites/proteins adjusted for a conservative correction for multiple comparisons at the level of factors estimated at 200 that will result from PCA analyses (α = 2.5 × 10–4). Based on effect sizes from previous studies, we have found a difference in mean (SD) levels between two groups of 0.32 (0.95) [76] as such, *N* = 109 in each group would provide 80% power. Thus, we will have sufficient power given this conservative estimate.

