#### Biospecimen population

A cohort of subjects participating in the primary trial will be included in the biospecimen analysis. Stool and blood serum samples will be collected at baseline and after the 6-month clinic-community intervention. Baseline samples will be from: (1) 100 obese adolescents (12–18 year olds); (2) 50 lean adolescent age- and sex-matched controls (12–18 year olds); (3) 100 obese children (5–11 year olds); and (4) 50 lean age- and sex-matched control children (5–11 year olds). Children and adolescents with obesity will be recruited through the primary study procedures until target sample size is met. Lean children will be recruited at the time of their well child visit, from the primary care clinic co-located with Healthy Lifestyles. Follow-up samples will only be collected from obese individuals.

We will build upon and expand resources that already exist within Duke University, namely, a biorepository of stool and blood serum samples from participants with obesity, aged 12–18, which has been established by a NIDDK-funded R24 grant (R24-DK110492). Analyses for Objective 2 will be conducted on samples from the expanded, shared biorepository. Figure 2 outlines patient samples that will come from the R24 cohort, and those that will come from this project.

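### Biospecimen power: at the stated α of 2.5 × 10⁻⁴, 109 per group gives about 11% power, not 80%, so the claim of sufficient power does not hold

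*Protocol article*

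**What the plan says.** In the protocol article, the section *Statistical analysis of biospecimens* justifies the size of the metabolite and protein analyses. It opens with "Power calculations for individual metabolites/proteins adjusted for a conservative correction for multiple comparisons", and describes this as a "conservative correction for multiple comparisons at the level of factors estimated at 200 that will result from PCA analyses", with α given as 2.5 × 10⁻⁴. The effect, taken from earlier work, is a difference of 0.32 with SD 0.95 between two groups. From these inputs it states that "109 in each group would provide 80% power" and closes with "Thus, we will have sufficient power given this conservative estimate".

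The same section says that the analyses themselves will use false discovery rate (FDR) adjustment, by platform or by number of factors. It does not say whether the power calculation is one- or two-sided.

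The section *Biospecimen population* fixes the baseline samples: 100 obese adolescents with 50 lean controls, and 100 obese children with "50 lean age- and sex-matched control children". Pooled over age, that is 200 obese and 100 lean.

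**The concern.** A standardised difference of about one third of an SD usually needs about 140 per group for 80% power at an ordinary two-sided 0.05. A requirement of 109 per group at an α 200 times smaller is therefore implausible on its face.

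The statement is the only power justification given for the omics work under Objective 2, one of the study's three objectives, and it claims adequacy outright. A reader who accepts it may take a null result for a metabolite or protein as evidence against an association of the assumed size. At the stated threshold, the study would in fact miss such an effect more than four times in five. Features that do pass would tend to have overestimated effects. The section also says these results will guide which stool samples go into the mouse experiments and which traits are monitored there.

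**Working it through.** **Inputs** (all from *Statistical analysis of biospecimens*, except the planned samples, which are from *Biospecimen population*)

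- Per-test α = 0.05/200 = 0.00025
- Difference 0.32, SD 0.95, so d = 0.32/0.95 = 0.3368
- Stated size and power: 109 per group, 80%
- Planned baseline samples: 100 + 100 = 200 obese, 50 + 50 = 100 lean

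**1. Can the plan's figure be reproduced at its stated α?**

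Normal formula for two equal groups: n = 2(z₁₋α/₂ + z₀.₈)²/d².

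With z for 1 − 0.000125 = 3.662 and z₀.₈ = 0.842: n = 2(4.504)²/0.3368² = 358 per group. The noncentral t distribution gives 361. The figure 109 is not reproduced.

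Other readings at α = 0.00025 also fail:

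| Reading | n for 80% power |
|---|---|
| Two groups, one-sided | 330 per group (normal), 333 (t) |
| Paired or one-sample, two-sided / one-sided | 179 / 165 |
| 0.95 read as a variance, two-sided / one-sided | 377 / 347 per group |

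**2. Where 109 probably comes from**

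One-sided α = 0.05 with no correction: n = 2(1.645 + 0.842)²/0.3368² = 108.98, which rounds up to 109. A two-sided α of 0.10 is the same calculation. Two-sided α = 0.05 needs 139 (normal) or 140 (t).

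**3. Power at 109 per group and α = 0.00025**

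Noncentrality: d√(109/2) = 2.487. Normal approximation: Φ(2.487 − 3.662) = Φ(−1.176) = 12.0%. By noncentral t it is 11.2%. One-sided it is 16.0% (normal) or 15.2% (t).

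**4. Power with the planned samples**

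Noncentrality at 200 versus 100: d√(200 × 100/300) = 2.750. Normal approximation: Φ(2.750 − 3.662) = 18.1%. By noncentral t it is 17.3%. One-sided by t it is 22.4%.

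Within one age group (100 versus 50), two-sided power by t is 3.9%.

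**5. What the planned samples can detect**

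At 200 versus 100, the difference detectable with 80% power is 4.504 × √(1/200 + 1/100) = 0.55 SD (normal), or 0.56 SD by t. The latter is 0.53 units at SD 0.95, and 0.53/0.32 ≈ 1.7 times the assumed effect.

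To reach significance at all, an observed difference must be at least about 3.662 × √(1/200 + 1/100) = 0.45 SD. This is already larger than the assumed 0.34 SD, so if the true effect is the assumed one, every feature that passes will overstate it.

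**6. Power with no multiplicity correction**

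Two-sided α = 0.05, by t: 70% at 109 versus 109, and 78% at 200 versus 100.

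**The case against.** The strongest objection is that α = 2.5 × 10⁻⁴ is not the planned decision rule. The analyses will use FDR adjustment, which can be less strict, so 17% is not necessarily the power the study will have. That is fair, and the miss rate given here holds only at the α the section itself uses. It does not rescue the claim. The section states its 80% at that α. If FDR is controlled at 5% (an assumption, as the article gives no level), the threshold for one feature cannot be looser than 0.05, and power is then at most 70% at 109 per group and 78% at 200 versus 100. At an FDR level of 10%, the outer limit at 200 versus 100 would be 86% (two-sided α = 0.10), but only if nearly every feature were declared significant.

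Several narrower points stand:

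- The 100 lean participants are fewer than 109, but the plan does not fall short of its own target in information. A 200:100 split equals 2 × 200 × 100/300 = 133 per group in precision, hence 17% rather than 11%. The finding does not rest on that shortfall.
- The 4% within one age group illustrates the subgroup size. The listed phenotype on children versus adolescents is a difference between comparisons, for which 4% is not the exact power.
- Objective 2 also covers continuous traits, prediction of response and change over time, which a two-group calculation does not address.
- The abstract already calls the microbiome and metabolomic outcomes exploratory, though the biospecimen section names four primary phenotypes and claims adequate power.
- The origin of 109 is inferred from an exact numerical match; the article does not state it.

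The primary BMI comparison and its sample size are unaffected.

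**Conclusion.** The concern holds. With the section's own inputs, 109 per group gives 11% power (12% by normal approximation, 15–16% if one-sided), not 80%. The requirement for 80% is about 361 per group, more than three times the stated figure. The planned 200 versus 100 gives about 17%. The conclusion of sufficient power is therefore wrong as written, on both the quoted and the planned numbers.

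This assumes a comparison of two independent means with a common SD of 0.95, two-sided unless noted, and takes the assumed effect as given, since its source is not available here. None of the readings tried at the stated α comes near 80% at 109; the closest, a one-sided paired test, gives 51% and does not fit a comparison described as between two groups.

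This must be corrected, because an explicit claim of adequacy for one of the study's objectives depends on it.

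**What to change.** Rewrite the power paragraph in *Statistical analysis of biospecimens* for the samples actually planned, for example: *With 200 obese and 100 lean participants and a two-sided α of 2.5 × 10⁻⁴, power is 17% for a difference of 0.32 (SD 0.95); the study has 80% power for differences of at least 0.56 SD.*

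Delete the closing sentence on sufficient power, and describe tests of single metabolites and proteins as exploratory.

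If FDR is the real decision rule, it is better to give power under that rule at the 200:100 allocation. State the FDR level and the assumed share of features with a true difference.

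The cost is wording only, plus a short recalculation if the FDR route is taken. No samples, visits or procedures change. The stated power becomes less favourable.
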